**7.3 Baseline / Randomisation Visit(s)**

The baseline/randomisation visit must occur no more than 4 weeks after the patient has successfully passed screening. The assessments will be conducted virtually by a research assistant.

The data as detailed below and in the study procedures table (Section 4.4) must be collected and all required procedures performed during the baseline/randomisation visit.

- Concomitant medications
- Vital signs (Blood pressure & heart rate) (Retrospective review of most recent reported measurements)
- Height, weight, BMI
- Patient Activation Measure (PAM-13)
- Clinical Frailty Scale
- Physical Health Questionnaire-4 (PHQ-4)
- Fatigue severity score (Chalder Fatigue Questionnaire)
- Work and social adjustment scale (WSAS Questionnaire)
- Functional capacity (sit-to-stand 60 to assess lower limb function)
- Global Physical Activity Questionnaire (GPAQ)
- Are you meeting current physical activity guidelines?
- Quality of life (KDQOL-36 and EQ5D-5L)
- Routine blood tests – Creatinine, Haemoglobin, CRP, IL-6, Albumin

**7.3.1 Treatment Procedures**

Participants will be randomised to receive either the Kidney Beam digital health intervention platform or will be randomised to waitlist for 12 weeks. At the end of the 12 weeks, all participants will be re-assessed before the waitlist participants are then offered the intervention. Participants in the non-waitlist group will be followed up after 6 months.

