**12 weeks Kidney Beam intervention**

**12 WEEK Assessment Visit**

**12 weeks:**

**Normal routine care**

History of COVID

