**Patient Information Sheet** **/ Consent Form**

Patient Information Sheet given to potential patients.

Consent form signed.

| PROCEDURE | | Screen Visit | End of 12 week pilot phase | Baseline/Randomisation Visit | Week 12 Visit | 6-month follow-up |
| --- | --- | --- | --- | --- | --- | --- |
| Patient information and informed consent | | X |  |  |  |  |
| Inclusion / Exclusion criteria | | X |  |  |  |  |
| Demographic data and medical history | | X |  |  |  |  |
| Height, weight, BMI, Clinical Frailty Scale | |  |  | X | X |  |
| **Vital signs (Blood pressure & heart rate) | |  |  | X | X |  |
| **Full blood count | |  |  | X | X |  |
| **Creatinine, CRP, eGFR, Hb, IL-6, Albumin from routine bloods | |  |  | X | X |  |
| Fatigue Severity Score (Chalder Fatigue questionnaire) | |  |  | X | X |  |
| Functional impairment (WSAS Questionnaire) | |  |  | X | X |  |
| Quality of life (KDQOL-36 and EQ5D-5L) | |  |  | X | X | X |
| Functional capacity (STS60) |  | |  | X | X |  |
| Global Physical Activity Questionnaire (GPAQ), and Physical Health Questionnaire (PHQ9) and additional questions on meeting current physical guidelines. |  | |  | X | X |  |
| Patient Activation Measure |  | |  | X | X |  |
| Qualitative Interview |  | | X |  | X |  |
| Adverse Events |  | |  | X | X |  |
| Kidney Beam platform metrics (PA mins and engagement) |  | |  |  | X | X |
| Healthcare utilisation questionnaire |  | |  | X | X | X |
| ***Post-COVID functional assessment tool questionnaire |  | |  | X | X | X |
| ****Digital health literacy screening tool | X | |  |  |  |  |
| ^*****^Hand grip Strength |  | |  | X | X |  |

** This procedure will only be a retrospective review of most recent available routine blood tests results and vital sign measurements. Results with date will be recorded by the study team. No new blood test will be collected from patient.

*** Only patients who had history of COVID at time of consent will be assessed for Post-COVID functional assessment tool questionnaire at Baseline.

****Only a sub set of patients from Kings College Hospital.

^*****^Only in a subset of patients at Newcastle NHS Trust

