**7.4 Kidney Beam Digital Health Intervention Platform**

Following the baseline assessment, those participants randomised to start immediately will be offered the Kidney Beam digital health intervention platform. Kidney Beam [https://beamfeelgood.com/home](about:blank) is a wellbeing digital health intervention platform that offers patients living with kidney disease a way to improve their physical activity and boost their mental health through live and on demand movement classes and expert educational videos, while remaining in their own home. Kidney Beam is led by specialist kidney professionals, including renal physiotherapists and renal counsellors, from a number of different NHS Trusts and backgrounds, as well as people living with kidney disease. The resource is aimed at anyone over 18, with any ability, any kidney condition, and at any stage of kidney disease.

Each participant will be encouraged to attend twice weekly virtual renal rehabilitation sessions led by a renal physiotherapist and a band 4 technical instructor in a group setting. This will be provided as a rolling 12-week programme and will include disease-specific education sessions. The sessions will be modelled on the King’s College Hospital Renal Rehabilitation programme.

Each participant will be encouraged to accumulate 150 mins/week of moderate intensity aerobic activity or 75 mins/week of vigorous activity, and to do some muscle resistance training on 2 days of the week. As well as partaking in renal rehabilitation classes, participants will be encouraged to engage with any other activities offered on Kidney Beam. This will be recorded on the platform and will be reported for each participant. At the end of the kick-start 12-week programme, participants will be encouraged to maintain and self-manage their activity via Kidney Beam.

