**7.6 6-month Follow-up**

The 6-month follow-up must occur 6 months (+4 weeks) after the participant has had their 12-week appointment. This will be conducted virtually via the Kidney Beam platform

- Quality of life (KDQOL-36 and EQ5D-5L)
- Kidney Beam platform metrics (physical activity mins and engagement)

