### 9. Assessment of Safety

### 9.1 Specification, Timing and Recording of Safety Parameters.

### Serious adverse events will be identified and reported to the sponsor. In addition, episodes of hospitalisation and other infection episodes will be documented.

###

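### Adverse events are scheduled at baseline and week 12 only, so the waitlist arm's whole programme and the non-waitlist arm's later platform use fall outside scheduled collection

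*Protocol*

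**What the plan says.** The row "Adverse Events" in the section 4.4 procedures table is marked at the baseline/randomisation and week 12 visits. Its 6-month cell is empty, while the same column is marked for quality of life, platform metrics and healthcare utilisation.

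Section 7.3.1 sets the order of events for the waitlist arm: "At the end of the 12 weeks, all participants will be re-assessed before the waitlist participants are then offered the intervention". The flowchart in section 4.3 then gives that arm "12 weeks Kidney Beam intervention". Later follow-up is stated for one arm only: "Participants in the non-waitlist group will be followed up after 6 months". Section 7.6 places that contact: "The 6-month follow-up must occur 6 months (+4 weeks) after the participant has had their 12-week appointment". It lists quality of life and platform metrics.

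Exposure in the non-waitlist arm does not stop at week 12. Section 7.4 says: "At the end of the kick-start 12-week programme, participants will be encouraged to maintain and self-manage their activity via Kidney Beam".

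On safety, section 9.1 says: "Serious adverse events will be identified and reported to the sponsor". It adds that hospitalisations and infection episodes will be documented. The section heading mentions timing, but the text as shown gives no period, visit or method.

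**The concern.** Adverse events are a listed secondary outcome (section 4.1.2). Section 10.3 says they will be collected and described, and section 12 has the data monitoring committee review safety at least every 4 months. The exclusion criteria treat recent cardiac events, arrhythmia, stroke and uncontrolled hypertension as relevant to taking part.

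If the table is followed as written, half of the randomised participants have adverse events solicited only while they are not receiving the intervention. Once they start it, no scheduled collection follows. For the other half, a remote visit takes place six months after week 12, but adverse events are not among its items. Non-serious events after week 12 then have no scheduled route into the data, and the trial's account of safety would rest on the first 12 weeks of one arm. That matters because section 4.1 says that the results are meant to support commissioning.

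**Working it through.** The protocol gives no exposure figure to reproduce. The check is a reading of the schedule, followed by simple person-time arithmetic.

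**Inputs**
- Total sample: 304 (section 10.1). The number follows from the plan's own figures: 212 / (1 − 0.30) = 302.9, or 303, against 304 stated. The sample size is not at issue here.
- Allocation 1:1 (section 6.4), so 304 / 2 = 152 per arm.
- Programme length: 12 weeks in each arm (sections 4.3 and 7.4).
- Later follow-up: 6 months after the week 12 appointment, taken as about 26 weeks (section 7.6).
- Share of the waitlist arm that never starts: not given. The range 0% to 30% is an assumption; the upper value borrows the dropout allowance in section 10.1.

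**Scheduled adverse event collections after week 12**
- Waitlist arm: 0. No later visit is stated for it.
- Non-waitlist arm: 0. The 6-month visit exists, but the cell is blank.

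**Planned 12-week programme exposure, full uptake**
- Inside scheduled collection (non-waitlist): 152 × 12 = 1,824 person-weeks.
- Outside it (waitlist): 152 × 12 = 1,824 person-weeks.
- Share outside: 1,824 / (1,824 + 1,824) = 1,824 / 3,648 = 50%.

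**If 30% of the waitlist arm never start**
- Outside: 152 × 0.70 × 12 = 1,277 person-weeks.
- Share outside: 1,277 / (1,824 + 1,277) = 1,277 / 3,101 = 41%.

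**Additional self-managed access, non-waitlist arm**
- At most 152 × 26 = 3,952 person-weeks after week 12. This is optional use, so it is kept apart from the shares above.

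**Could another item fill the gap?**
- The table ticks the healthcare utilisation questionnaire at 6 months. Section 7.3.8 gives it a 3-month recall and a costing purpose. With the visit 6 months after week 12, about 6 − 3 = 3 months are not covered even for healthcare use. Section 7.6 leaves it off its list, and the waitlist arm has no stated 6-month visit.
- Section 6.5 keeps withdrawn participants under follow-up for adverse events, but adds no collection point for those who stay in.
- The final interviews in section 7.7 reach up to 30 people and ask about experience. They are not a safety assessment.

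**The case against.** The strongest reply is that the protocol does have safety reporting after week 12. Section 9.1 commits to reporting serious events and documenting hospitalisations and infections, and neither commitment ends at week 12. The contents page also lists a section 9.2 on recording and reporting adverse events. Its text is not in the material supplied and may have been lost in extraction, so a reporting period and route could be stated there. This stands. A reader might infer that nothing at all is reported after week 12, or that the protocol fails to set a period for serious event reporting; the documents at hand do not support either.

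Two other strong readings also fail. One is that participants exercise unsupervised and out of contact. Section 7.4 describes twice-weekly live group sessions led by a renal physiotherapist, and participants remain patients of their kidney units. What is missing is a scheduled adverse event assessment, not every chance of noticing an event. The other is that most of the trial's exposure goes unobserved. Adding the optional access does give (1,824 + 3,952) / (3,648 + 3,952) = 5,776 / 7,600 = 76%, but this assumes no dropout, full waitlist uptake, and six months of self-managed access equal to programme exposure.

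The silence of section 7.6 is weak evidence by itself, because the lists in sections 7.3 and 7.5 also omit adverse events at visits where the table ticks them. The blank table cell carries the point.

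Finally, waitlist use after week 12 follows the randomised comparison, so events there add description only. That is true and limits the weight of the point. It does not explain why a visit that already takes place omits a listed outcome.

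**Conclusion.** The point holds as a gap in the stated schedule. No adverse event collection is scheduled after week 12 in either arm, although the waitlist arm's programme begins then and the non-waitlist arm is encouraged to continue. Between about 41% and 50% of planned 12-week programme exposure lies outside scheduled collection, with optional later access by the non-waitlist arm on top. The range assumes 152 per arm, a full 12 weeks for those who start, no loss in the non-waitlist arm, and 0% to 30% of the waitlist arm never starting.

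The comparison of arms over weeks 0 to 12 is unaffected, as are the primary outcome and the sample size. What suffers is the description of safety over all use of the platform, mainly for non-serious events. This is an inexpensive improvement to the plan, not a flaw that threatens its main conclusion.

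**What to change.** - Tick adverse events at the existing 6-month follow-up in the section 4.4 table and add them to the section 7.6 list.
- Reconcile the table and section 7.6 with section 9.1, and with section 9.2 if it exists in the full document, so that all give the same collection points.
- Report events from weeks 0 to 12 by randomised arm. Report later events separately and descriptively, without a between-arm comparison.
- Where feasible, send waitlist participants a short remote adverse event questionnaire at the end of their 12-week programme. This is more debatable than the other items because it adds a contact that the protocol does not now have.

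The cost is a few items at a remote visit that already takes place, minor data handling, and, if the last item is adopted, one short questionnaire per waitlist participant. Treatment, endpoint and sample size do not change.

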**7.3.2 Fatigue**

The Chalder Fatigue Questionnaire is an 11-item questionnaire measuring the severity of physical and mental fatigue on two separate subscales (47). Seven items represent physical fatigue (items 1-7) and 4 represent mental fatigue (items 8-11). Each item is scored; better than usual (0), no worse than usual (1), worse than usual (2) and much worse than usual (3). The ratings of items are added together to calculate the total score (range = 0-33) where high scores represent greater levels of fatigue. This questionnaire has previously been used as a measure of fatigue in HD patients as well as other long-term medical conditions. Internal reliability of the total fatigue score is high among renal patients (>.90).

**7.3.3 *Functional impairment and physical activity***

The Work and Social Adjustment Scale (WSAS) is a valid and reliable self-report scale of functional impairment attributable to an identified problem (in this case fatigue) (48,49). The scale consists of five items that correspond to impairment in work, home management, social activities, private leisure activities and relationships. Each item is rated on a 9-point scale ranging from 0 (not at all a problem) to 8 (very seriously impaired), with high scores indicating greater impairment (α=0 .90).

7.3.4 *Physical function and physical activity*

*Sit-to-Stand 60 Seconds (STS60):* We will also use the STS60 to provide a measure of muscle endurance, another aspect of physical performance (50,51). The STS60 is a commonly used and simple assessment of muscle endurance, an aspect of physical performance that directly influences ability to carry out daily tasks. This test requires the patient to stand up from a chair and sit back down again and counts the amount of repetitions completed in 60 seconds. Participants will be asked if they are meeting current physical activity guidelines with the following 3 questions: 1) Do you do strength training on 2 or more days of the week? 2) Do you do 150 mins or more of moderate intensity physical activity per week? 3) Do you do 75 mins or more of vigorous physical activity per week?

***7.3.5 Patient Activation Measure (PAM-13)***

The PAM-13 is a validated tool of 13 questions which assesses a patient’s knowledge, skills and confidence in managing their own health. The PAM-13 has demonstrated good internal consistency as well as adequate reliability and validity (52,53). Answers are weighted and combined to provide a score on a scale from 0 to 100. A score is generated where participants have answered ≥10 questions. The PAM allows respondents to be categorized into one of four levels with lower levels indicating low activation and higher levels indicating high activation): Level 1 (<47.0), disengagement and disbelief about one’s own role in self-management; Level 2 (47.1–55.1), increasing awareness, confidence, and knowledge in self-management tasks; Level 3 (55.2–67), readiness and taking action; and Level 4 (>67.1), sustainment.

***7.3.6 Clinical Frailty Score***

The Clinical Frailty Scale (CFS), a risk stratification tool which grades  frailty level from 1 (very fit) to 9 (terminally ill) using the standardised qualifiers, and has been validated for use in a range of CKD populations, will be used to identify the frailty status of participants at baseline (64).

***7.3.7 Physical Health Questionnaire-4 (PHQ-4)***

The Patient-Health Questionnaire-4 (PHQ-4) is an ultra-brief screener for depression and anxiety (Kroenke, et al 2009). The measure has 4 items, two each from the PHQ-2 and GAD-2. This brief screener has good internal reliability and construct validity. A PHQ-4 total score of ≥6 or symptom score ≥3 on the depression or anxiety items of PHQ-4 represent likely clinical levels of depression or anxiety (Löwe et al, 2010)

***7.3.8 Healthcare Utilisation***

A healthcare utilisation questionnaire will be administered in order to assess the extent of healthcare usage over the previous 3 months including but not limited to inpatient services, outpatient services, community and general practitioner services and the emergency services. This will provide a basis on which the costs associated with setting up and maintaining Kidney BEAM and its content can be compared to the potential benefits such as keeping patients fitter, more active, out of hospital for longer and in some cases, able to work.

**7.4 Kidney Beam Digital Health Intervention Platform**

Following the baseline assessment, those participants randomised to start immediately will be offered the Kidney Beam digital health intervention platform. Kidney Beam [https://beamfeelgood.com/home](about:blank) is a wellbeing digital health intervention platform that offers patients living with kidney disease a way to improve their physical activity and boost their mental health through live and on demand movement classes and expert educational videos, while remaining in their own home. Kidney Beam is led by specialist kidney professionals, including renal physiotherapists and renal counsellors, from a number of different NHS Trusts and backgrounds, as well as people living with kidney disease. The resource is aimed at anyone over 18, with any ability, any kidney condition, and at any stage of kidney disease.

Each participant will be encouraged to attend twice weekly virtual renal rehabilitation sessions led by a renal physiotherapist and a band 4 technical instructor in a group setting. This will be provided as a rolling 12-week programme and will include disease-specific education sessions. The sessions will be modelled on the King’s College Hospital Renal Rehabilitation programme.

Each participant will be encouraged to accumulate 150 mins/week of moderate intensity aerobic activity or 75 mins/week of vigorous activity, and to do some muscle resistance training on 2 days of the week. As well as partaking in renal rehabilitation classes, participants will be encouraged to engage with any other activities offered on Kidney Beam. This will be recorded on the platform and will be reported for each participant. At the end of the kick-start 12-week programme, participants will be encouraged to maintain and self-manage their activity via Kidney Beam.

**7.5 Week 12 Appointment**

The week 12 appointment must occur 12 weeks (+4 weeks) after the patient has had their baseline appointment.

The data as detailed below and in the Trial Flowchart must be collected and all required procedures performed during the 12-week appointment.

- Concomitant medications
- Vital signs (Blood pressure & heart rate) (Retrospective review of most recent reported measurements)
- Height, weight, BMI
- Patient Activation Measure (PAM)
- Clinical Frailty Score
- Physical Health Questionnaire-4 (PHQ-4)
- Fatigue severity score (Chalder Fatigue Questionnaire)
- Functional Impairment (WSAS Questionnaire)
- Functional capacity (sit-to-stand 60 to assess lower limb function)
- Global Physical Activity Questionnaire (GPAQ)
- Are you meeting current physical activity guidelines?
- Quality of life (KDQOL-36 and EQ5D-5L)

**7.6 6-month Follow-up**

The 6-month follow-up must occur 6 months (+4 weeks) after the participant has had their 12-week appointment. This will be conducted virtually via the Kidney Beam platform

- Quality of life (KDQOL-36 and EQ5D-5L)
- Kidney Beam platform metrics (physical activity mins and engagement)

**7.7** **Qualitative Exploration of Patient Experience and Acceptability**

Semi-structured interviews will be used to gather qualitative data as they offer an open and flexible method for exploring the participants’ individual experiences in-depth.

Interviews will occur at two time points:

- At the end of the internal pilot phase to further understand the acceptability of the platform and to contextualise and expand upon the feasibility outcomes (‘pilot interviews’).
- On completion or withdrawal from the trial to explore the impact of the intervention upon participants’ experiences of living with kidney disease, to contextualise the results of the trial and to understand the potential longer-term acceptability of using BEAM (‘final interviews’).

If time and resources permit, further exploration of maintenance and factor influencing the sustainability of the programme will be undertaken at the long-term follow-up time point.

For all interviews the inclusion and exclusion criteria for the qualitative component will mirror that of the main trial, although participants who are unable to speak English will be excluded due to challenges relating to interpretation and translation. To reduce potential problems with recall bias, participants will be interviewed as close to the end of the pilot phase, or the completion of the full trial.

**Sampling and sample size**

Maximum variation sampling will initially be used to ensure that participants are purposefully different from each other (54). For the pilot interviews primary importance will be given sampling participants who have had a diverse range of engagement with the BEAM platform to provide greater insight into its acceptability. For final interviews, primary importance will be given to ensuring good representation of participants living with different stages of CKD and/or receiving different forms of renal replacement therapy from both arms of the trial. For all interviews, other important characteristics (e.g. age, gender, ethnicity) will be monitored on an ongoing basis as recruitment and analysis progresses (55).

For the pilot interviews, up to 15 participants from the intervention arm will be recruited, although information power will be assessed throughout and the final sample size determined by the quality of the data and its ability to address the qualitaitve aims (56). For the final interviews, up to 30 participants will be recruited in total, from each arm of the trial. Again, data collection will cease at the point where information power is achieved.

Topic guides for each interview will be developed in advance of the study in partnership with the trial steering committee and PPI representatives, guided by the RE-AIM framework, which is designed to enhance the quality, speed, and public health impact of efforts to translate research into practice (57).The first three interviews at each phase will act as pilots (but will be included within the overall analyses). Interviews will be conducted by an experienced qualitative researcher at an appointment separate from the other trial assessments, via telephone or video link. Family members or other relatives may be present during the interview if the participant wishes.

During the interviews, the researcher will introduce the process, explaining the background, how the interview will proceed, and details of audio-recording and note-taking. Patients will be reassured about the preservation of their anonymity and confidentiality as well as being given the opportunity to ask questions before audio-recording commences. Interviews are expected to last approximately 60 minutes. At the end of each interview, participants will be given another opportunity to ask questions, or seek clarification and the voluntary nature of their participation will be re-iterated. Should any participant request further information or highlight any concerns during the interview then these will be discussed with the Principal Investigator at their recruiting site, for appropriate onward referral as required. All participants will be made fully aware of the contact details for the research team, should they have any concerns following the interview.

The recorded interviews will be professionally transcribed verbatim. Transcripts will not include any-identifying information; individual’s names and personal details will not be included in the completed transcripts but will be recorded and stored separately. Similarly, any written notes taken during the interviews will not include any identifiable personal data.

Thematic analysis of all sets of interviews will be conducted alongside data collection according to the methods outlined by Braun and Clarke (2006) (58). Briefly, researchers with qualitative research experience will independently familiarise themselves with the data and generate initial codes inductively from the data. These codes will then be collated into initial themes, which will be reviewed by the multidisciplinary research team and the PPI group, until they are refined. The researchers will move back and forth between stages as new themes are generated and relationships recognised. Participants' narratives across interviews will be compared and contrasted. NVivo (QSR International) software will be used to manage the qualitative data and to facilitate analysis.

